##### Challenging Experience Questionnaire

- **0 – none; not at all**
- **1 – so slight cannot decide**
- **2 – slight**
- **3 – moderate**
- **4 – strong**
- **5 – extreme (more than ever before in my life)**
- ______ 1. Isolation and loneliness
- ______ 2. Sadness
- ______ 3. Feeling my heart beating
- ______ 4. I had the feeling something horrible would happen
- ______ 5. Feeling my body shake/tremble
- ______ 6. Feelings of grief
- ______ 7. Experience of fear
- ______ 8. Fear that I might lose my mind or go insane
- ______ 9. I felt like crying
- ______ 10. Feeling of isolation from people and things
- ______ 11. Feelings of despair
- ______ 12. I had the feeling that people were plotting against me
- ______ 13. I was afraid that the state I was in would last forever
- ______ 14. Anxiousness
- ______ 15. I felt shaky inside
- ______ 16. I had the profound experience of my own death
- ______ 17. I felt my heart beating irregularly or skipping beats
- ______ 18. Pressure or weight in my chest or abdomen
- ______ 19. I experienced a decreased sense of sanity
- ______ 20. I felt as if I was dead or dying
- ______ 21. Panic
- ______ 22. Experience of antagonism toward people around me
- ______ 23. Despair
- ______ 24. I felt isolated from everything and everyone
- ______ 25. Emotional and/or physical suffering
- ______ 26. I felt frightened

##### Watts’ Connectedness Scale (WCS)

**Reference**

**Instructions**

Reflecting on how you have felt over the past 2 weeks, please rate the following items on a scale from **'Not at all' to 'Entirely'** according to how you have felt over this time period. Please answer every item, even if you are unsure or feel the item is unclear or poorly worded. Drag the indicator to a position on the scale that shows how much you agree or disagree with each of the following statements.

Response format

Each item is rated on a 0 – 100 visual analogue scale with the anchors 0 = Not at all, 100 = Entirely

| Final items  *1. I have felt trapped in my mind.* |
| --- |
| *2. My mind has felt connected to my heart/emotion.* |
| *3. I have felt connected to my senses (touch, taste, sight smell, hearing).* |
| *4. I have felt connected to a range of emotions.* |
| *5. If I had chosen to, I could have ‘sat with’ painful memories.* |
| *6. I have felt connected to my body.* |
| *7. I have been able to fully experience emotion, whether positive or negative.* |
| *8. I have felt alone.* |
| *9. I have felt connected to friends and/or family.* |
| *10. I have felt connected to a community.* |
| *11. I have felt connected to all humanity.* |
| *12. I have felt unwelcome amongst others.* |
| *13. I have felt separate from the world around me.* |
| *14. I have felt connected to a purpose in life.* |
| *15. I have felt connected to nature.* |
| *16. I have felt connected to a spiritual essence (in the secular or religious sense).* |
| *17. I have felt connected to a source of universal love.* |
| *18. I have seen things from a broad perspective, ‘the bigger picture’.* |
| *19. I have felt that everything is interconnected.* |

Scoring

Connectedness to Self (CTS): (WCS2 + WCS3 + WCS4 + WCS5 + WCS6 + WCS7) / 6

Connectedness to Others (CTO): ((100 – WCS1) + (100 – WCS8) + WCS9 + WCS10 + (100 – WCS12) + (100 – WCS13)) / 6

Connectedness to World (CTW): (WCS11 + WCS14 + WCS15 + WCS16 + WCS17 + WCS18 + WCS19) / 7

General Connectedness (WCS): (CTS + CTO + CTW) / 3

# PAPR Preference/ Expectancy

Subject ID#:

Subject Initials:

Date: / /

Visit: Screen

# VISUAL ANALOGUE SCALE

Please indicate your **opinion** on the following questions.

1. On a scale of 0 to 100, how **effective** would psilocybin-assisted therapy plus MBSR

be in treating your symptoms? (circle one)

0

10

20

30

40

50

60

70

80

90

Not

Effective

100

Very Effective

2. On a scale of 0 to 100, how **effective** would just MBSR

be in treating your symptoms? (circle one)

0

10

20

30

40

50

60

70

80

90

Not

Effective

100

Very Effective

3. Which do you think will be **more** effective in treating your symptoms? (circle one)

5

Psilocybin

More Effective

4

3

2

1

0

Equally Effective

1

2

3

4 5

MBSR

More Effective

4. Which therapy would you **prefer** for treating your symptoms? (circle one)

MBSR

5

4

3

2

1

0

No Preference

1

2

3

4

5

Prefer psilocybin

Prefer

Staff Initials:

Database entry by: on / /

**PAPR Credibility/Expectancy**

**Subject ID#:**

**Subject Initials:**

**Date: / /**

**Visit: __**

CREDIBILITY / EXPECTANCY QUESTIONNAIRE

We would like you to indicate below how much you believe, **right now**, that the therapy you are going to recieve will help to reduce your anxiety. Belief usually has two aspects to it: (1) what one **thinks** will happen and (2) what one **feels** will happen. Sometimes these are similar; sometimes they are different.

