## Randomization and study arm assignment

Participants who meet eligibility criteria and have consented and enrolled in the study will be randomized to either the MBSR Arm or the MBSR + PAP arm using a randomization plan generated by the SAS code, PROC plan. The study will be open label and participants will be informed as to study arm assignment prior to the first MBSR session. There will be rolling enrollment in trial participation up until the cut-off registration date prior to each MBSR course starting date. Each arm will be run independently given likely variation on numbers of participants willing to complete each study arm however efforts will be made to run both arms concurrently depending on recruitment. While the MBSR only arm can be completed on an individual basis for each participant the MBSR + PAP arm includes group-based psilocybin-assisted therapy interventions which requires 2-5 participants per MBSR cohort. We will leave open the option of running group PAP sessions for a cohort of only 2 participants however will have a goal participant number per cohort of 4 with the possibility of running up to 5 participants per cohort through this arm. To assess expectancy effects on treatment response participants will be administered expectancy scales prior to randomization to assess preference as well as post randomization to assess credibility.

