## Efficacy

The efficacy of the study therapy will be determined by the change in depression scores as measured by the QIDS-SR (primary) and burnout scores as measured by the MBI-HSS(MP) (secondary).

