**Set 1**: Answer in terms of what you **think**

1. At this point, how **logical** does the therapy offered to you seem?

1

2

3

4

5

somewhat logical

6

7

8

9

not at all logical

very logical

2. At this point, how successfully do you **think** this treatment will be in reducing your symptoms?

1

2

3

4

5

somewhat useful

6

7

8

not at all useful

9

very useful

3. How **confident** would you be in recommending this treatment to a friend who experiences similar problems?

1

2

3

4

5

somewhat confident

6

7

8

9

not at all confident

very confident

4. By the end of the therapy period, how much improvement in your symptoms do you **think** will occur?

0% 10% 20% 30% 40% 50% 60% 70% 80% 90% 100%

**Set 2**: Answer in terms of what you really and truly **feel** about the therapy and its likely success.

1. At this point, how much do you really **feel** that therapy will help you to reduce your symptoms?

1

not at all

2

3

4

5

somewhat

6

7

8 9

very much

2. By the end of the therapy period, how much improvement in your symptoms do you really **feel** will occur?

0% 10% 20% 30% 40% 50% 60% 70% 80% 90% 100%

Staff Initials:

Database entry by: on / /

v.Jan2011 Page 1 of 1

1. Follow up measures to be administered 14 days (+/- 3) and 180 days (+/-7) after final MBSR session in week 8. [↑](#endnote-ref-1)
2. Vital signs include systolic and diastolic blood pressure, heart rate, respiratory rate, pulse oximetry, weight. Weight captured at screening only. [↑](#endnote-ref-2)
3. On day of psilocybin administration vital signs will be assessed approx. 10 min before dosing and at 30, 50, 90, 120, 180, 240, 300, and 360 minutes after psilocybin administration. [↑](#endnote-ref-3)
4. All Questionnaires scheduled for MBSR Week 1 to be administered prior to the first MBSR session. [↑](#endnote-ref-4)
5. Integration sessions #1 and #2 both included in this week for the PAP + MBSR arm. Adverse event collection, suicidality, concomitant meds will all be assessed x 2 during this week for the PAP+MBSR arm. [↑](#endnote-ref-5)
6. Adverse event collection will occur during all 3 preparatory sessions and all 3 integration sessions for the PAP+MBSR arm. [↑](#endnote-ref-6)

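### The post-randomisation credibility/expectancy form names anxiety in its instruction, leaving it unclear whether answers concern anxiety or the trial's targets, depression and burnout

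*Protocol*

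**What the plan says.** Section 9.2 of the protocol (Randomization and study arm assignment) states the design and the purpose of the expectancy measures. On blinding: "The study will be open label and participants will be informed as to study arm assignment prior to the first MBSR session". On purpose: "To assess expectancy effects on treatment response participants will be administered expectancy scales prior to randomization", with a second scale after randomisation. The Schedule of Events places expectancy questionnaires at screening and in week 1, and its footnote says that week 1 questionnaires come before the first MBSR session.

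The post-randomisation instrument is the PAPR Credibility/Expectancy form, printed at the end of the protocol. Its instruction asks how much the participant believes, at that moment, that "the therapy you are going to recieve will help to reduce your anxiety". Six items follow in two sets, one on what the participant thinks and one on what the participant feels.

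Section 11.2 (Efficacy) says that efficacy is determined by "the change in depression scores as measured by the QIDS-SR (primary) and burnout scores as measured by the MBI-HSS(MP) (secondary". Section 10.6 (Response Assessment) names the same two instruments. The inclusion criteria in section 5.1 require a PHQ-9 score of at least 10, a DSM-5 depressive disorder and the working definition of burnout. They contain no anxiety criterion.

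**The concern.** The form exists to help interpret treatment response, and response in this trial means change in depression and burnout. The instruction points participants to a different symptom. The items do not put this right, because none of them names depression or burnout. Some participants may answer about their anxiety and others about their low mood or exhaustion at work, and nothing on the completed form shows which.

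This matters more here than it would in a blinded trial. Participants know their arm and the primary outcome is a self-report depression scale, so expectancy is an obvious rival explanation for a difference between arms. This form is the only expectancy measure taken after allocation is known. Expectancy between allocation and the start of treatment can be recorded only in that window, so an ambiguous answer cannot be replaced later.

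**Working it through.** No arithmetic on power, alpha or sample size applies. The check sets the form's wording beside the rest of the protocol.

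**Step 1: the form itself.** The symptom each part names:

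| Part of the form | What it asks | Symptom named |
| --- | --- | --- |
| Instruction | Belief that therapy will help | Anxiety |
| Set 1, item 1 | How logical the therapy seems | None |
| Set 1, item 2 | How successful "this treatment will be in reducing your symptoms" | Unspecified symptoms |
| Set 1, item 3 | Confidence in recommending it to a friend | Similar problems, unspecified |
| Set 1, item 4 | "By the end of the therapy period, how much improvement in your symptoms do you" think will occur | Unspecified symptoms |
| Set 2, item 1 | How much the participant feels "that therapy will help you to reduce your symptoms" | Unspecified symptoms |
| Set 2, item 2 | As Set 1, item 4, but for what is felt | Unspecified symptoms |

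Count over the six scored items: anxiety 0, depression 0, burnout 0, unspecified symptoms 4, similar problems 1, no symptom 1 (4 + 1 + 1 = 6). Anxiety appears once on the form, in the instruction, and is the only symptom the form names.

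**Step 2: the trial's target.** Entry (section 5.1), response assessment (section 10.6) and efficacy (section 11.2) all rest on depression, burnout or both.

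**Step 3: anxiety elsewhere in the protocol.** One secondary objective in the Study Summary covers long-term effects on both depression and anxiety symptoms. The Storyline battery in the appendix includes the GAD-7, and section 1.3 schedules that battery at baseline, at 2 weeks and at 6 months after the intervention. Section 1.2, however, lists secondary endpoints for burnout, demoralization, post-traumatic stress and connectedness, and the secondary analyses in section 12.2 give anxiety no outcome of its own.

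**Step 4: the pre-randomisation form.** The Preference/Expectancy form asks about treating the participant's symptoms and contains no anxiety wording. It is not in error.

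**Step 5: use in the analysis.** The primary model in section 12.2 contains treatment, time, their interaction and a participant effect. It has no expectancy term, so the primary contrast does not depend on this form.

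Taken together, the instruction conflicts with the form's own generic items and with the trial's target. The result is an ambiguous score.

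**The case against.** The strongest reply is that the scored items decide what is measured, and none of them says anxiety. Participants have been screened and enrolled for depression and burnout, so they would naturally read their symptoms as those. Anxiety is also not foreign to the trial, given the Study Summary objective and the GAD-7. The screening form already collects 0 to 100 effectiveness ratings for both treatments without the anxiety wording, so each participant has a rating for the arm later assigned. Section 9.2 describes the scales as "expectancy scales prior to randomization to assess preference as well as post randomization to assess credibility", so the later form is there for credibility, and its items on logic and recommendation name no symptom. Finally, section 12 specifies no analysis that uses the form.

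Much of this stands. It rules out a stronger reading that a reader might reach, namely that the form fails to measure the relevant expectancy at all. Generic items can be answered about depression and burnout, and some participants will answer them that way.

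Three things remain. The form never mentions depression or burnout, so the instruction is the only text on it that tells participants which symptoms are meant. A rating given before randomisation does not show what a participant expects after learning the allocation. And a mention of anxiety in one synopsis objective does not explain why the form leaves out both main outcomes.

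**Conclusion.** The point holds as a wording error in a data-collection instrument. The instruction makes the only post-allocation expectancy score ambiguous as to its target and so weakens the stated purpose of assessing expectancy effects on treatment response. The wording and the item count are certain. How many participants would be steered by the instruction is unknown.

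A reader might infer two further things that the documents do not support:

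- **A quantified loss of information.** This would need the correlation between expectancy about anxiety and expectancy about depression and burnout. The protocol gives none. It would also need every participant to follow the instruction literally, which the generic items make doubtful.
- **Bias in the estimated psilocybin effect.** The primary contrast does not use the form. Bias from expectancy, if present, comes from open-label self-report and not from this word. Credibility rated after allocation may itself depend on allocation, so even a correctly worded form would not let an adjustment simply remove that bias.

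The absence of an expectancy analysis from section 12 is not part of the point, because it may be set out in an analysis plan that was not available.

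The correction is still worth making. It changes what participants are told to rate, costs very little, and concerns data that cannot be collected again after treatment begins.

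**What to change.** In the instruction of the PAPR Credibility/Expectancy form, replace *your anxiety* with *your symptoms of depression and burnout*. The minimum change is *your symptoms*, which would match the form's own items and the pre-randomisation form. Naming the two targets is preferable because it removes the ambiguity.

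Submit the revised form to the IRB before further participants complete it. Flag in the database any forms completed under the present wording, so that they can be identified in whatever expectancy analysis is done. The Preference/Expectancy form needs no change.

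The cost is a few words and one IRB submission. There is no added burden on participants and no effect on sample size or on the primary analysis.

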**Set 1**: Answer in terms of what you **think**

1. At this point, how **logical** does the therapy offered to you seem?

1

2

3

4

5

somewhat logical

6

7

8

9

not at all logical

very logical

2. At this point, how successfully do you **think** this treatment will be in reducing your symptoms?

1

2

3

4

5

somewhat useful

6

7

8

not at all useful

9

very useful

3. How **confident** would you be in recommending this treatment to a friend who experiences similar problems?

1

2

3

4

5

somewhat confident

6

7

8

9

not at all confident

very confident

4. By the end of the therapy period, how much improvement in your symptoms do you **think** will occur?

0% 10% 20% 30% 40% 50% 60% 70% 80% 90% 100%

**Set 2**: Answer in terms of what you really and truly **feel** about the therapy and its likely success.

1. At this point, how much do you really **feel** that therapy will help you to reduce your symptoms?

1

not at all

2

3

4

5

somewhat

6

7

8 9

very much

2. By the end of the therapy period, how much improvement in your symptoms do you really **feel** will occur?

0% 10% 20% 30% 40% 50% 60% 70% 80% 90% 100%

Staff Initials:

Database entry by: on / /

v.Jan2011 Page 1 of 1

1. Follow up measures to be administered 14 days (+/- 3) and 180 days (+/-7) after final MBSR session in week 8. [↑](#endnote-ref-1)
2. Vital signs include systolic and diastolic blood pressure, heart rate, respiratory rate, pulse oximetry, weight. Weight captured at screening only. [↑](#endnote-ref-2)
3. On day of psilocybin administration vital signs will be assessed approx. 10 min before dosing and at 30, 50, 90, 120, 180, 240, 300, and 360 minutes after psilocybin administration. [↑](#endnote-ref-3)
4. All Questionnaires scheduled for MBSR Week 1 to be administered prior to the first MBSR session. [↑](#endnote-ref-4)
5. Integration sessions #1 and #2 both included in this week for the PAP + MBSR arm. Adverse event collection, suicidality, concomitant meds will all be assessed x 2 during this week for the PAP+MBSR arm. [↑](#endnote-ref-5)
6. Adverse event collection will occur during all 3 preparatory sessions and all 3 integration sessions for the PAP+MBSR arm. [↑](#endnote-ref-6)
